**Methods:**

This study utilized a randomized controlled trial design, where eligible patients diagnosed with AARS were, randomly assigned (1:1) to either a treatment group (gentle manipulative technique combined with continuous traction) or a control group (traction plus cervical collar immobilization). The treatment group received treatment twice daily, five days per week, for two weeks. The control group received the same traction protocol but wore a neck brace immediately after each traction treatment. The primary outcome measure was musculoskeletal ultrasound (MUSU) findings, while secondary outcomes include Visual Analogue Scale (VAS) pain scores and Neck Disability Index (NDI) scores. Both groups were assessed at baseline, post-treatment, two weeks, and six months after treatment.

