##### Follow-up observation

Assessment after treatment at the two-week mark, and again during a follow-up observation up evaluations will occur two weeks and six months after completion of treatment to assess symptom recurrence or sustained improvement.

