### Statistical methods

Sample size estimation is based on comparisons of two proportions in a fully randomized design following He Yan's work, “Statistics in Traditional Chinese Medicine.” In this framework, the variable p represents the combined rate, while p1 and p2 indicate the known rates for each group. The required sample size for each group is denoted as n. The literature establishes the maximum efficacy rate at 93.5% and the minimum efficacy rate at 73.6%. Assuming equal sample sizes for both groups, *p* can be calculated as the average of *p*1 and *p*2, formulated as *p* = (*p*1 + *p*2)/2, with *q* defined as 1 − *p*. The formula for determining the necessary sample size is *n* = 8*pq*/(*p*1 − *p*2)^2^. Based on this calculation, *n* is estimated to be 28. Considering a projected dropout rate of 15%, the minimum number of observations needed for each group is adjusted to 32 participants to account for dropout, which is derived by dividing 28 by (1–0.15). To further improve the accuracy of the trial data and the resulting statistical outcomes, the sample size will ultimately be increased to 35 participants per group to enhance the reliability of the statistical results.

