### Statistical analysis

All data will be analyzed using SPSS version 22.0 software. Categorical data will be summarized as frequencies or percentages and compared using Chi-square tests. Ordinal data will be analyzed using rank-sum tests. For measurement data that follow a normal distribution and demonstrate homogeneity of variance, results will be presented as mean ± standard deviation (x ± s). Independent samples t-tests will be used for between-group comparisons, paired-sample t-tests for within-group comparisons. Non-normally distributed data will be analyzed with nonparametric rank-sum tests. A *P*-value < 0.05 will be considered statistically significant.

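### Follow-up is meant to show sustained improvement, but the named two-sample and paired tests give no between-arm estimate of how the effect changes, and dropout could bias the six-month difference

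*Protocol article*

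**What the plan says.** The abstract sets out the assessment times: "Both groups were assessed at baseline, post-treatment, two weeks, and six months after treatment". That is one baseline and three post-treatment occasions. The Follow-up observation section says what the later visits are for: evaluations take place "two weeks and six months after completion of treatment to assess symptom recurrence or sustained improvement".

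The Statistical analysis section covers all data and names the tests. For measurement data: "Independent samples t-tests will be used for between-group comparisons, paired-sample t-tests for within-group comparisons". Where normality fails: "Non-normally distributed data will be analyzed with nonparametric rank-sum tests". For categories: "Categorical data will be summarized as frequencies or percentages and compared using Chi-square tests". The threshold is P below 0.05.

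Dropout appears once, in the sample-size paragraph ("Considering a projected dropout rate of 15", in per cent), where it only inflates the number per group. It is not tied to a visit.

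The article names no group-by-time comparison and no model over visits.

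**The concern.** A plan that measures each child three times after treatment, in order to learn whether improvement lasts, needs a comparison between arms that spans those visits. The tests named each take two samples or two time points.

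Two things are at stake:

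- **Interpretation.** Without a between-arm estimate of change, a reader may be told that the benefit was sustained because P was below 0.05 at both visits, or lost because it was below 0.05 at one and above it at the other. Neither pattern tests whether the effect changed. Within-arm paired tests do not help, because children may improve or relapse in both arms for reasons unrelated to the allocated treatment.
- **Bias.** A t-test needs the value at its own visit. A child who misses six months contributes nothing to that comparison, even though earlier scores are on file. Treatment is open, and the arms differ in burden (manual therapy against a collar worn as long as tolerated), so dropout that differs by arm and by progress is plausible.

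**Working it through.** **1. The plan's own figures.** The sample-size paragraph uses rates of 93.5% and 73.6%.

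- p = (0.935 + 0.736)/2 = 0.8355 and q = 0.1645.
- n = 8pq/(p1 − p2)² = 8 × 0.8355 × 0.1645/0.199² = 27.76, so 28 as stated.
- 28/0.85 = 32.94, so 33 where the article says 32. The final 35 per group covers the difference.
- If the whole 15% were missing at six months, 35 × 0.85 = 29.75, about 30 per arm, would remain.

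**2. What each named test estimates.**

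| Test | Question answered | Randomised comparison? | Change over follow-up? |
|---|---|---|---|
| Two-sample (t or rank-sum) at six months | Do the arms differ then? | Yes, subject to dropout | No |
| Paired, baseline to a later visit | Did this arm improve? | No | No |
| Paired, end of treatment to six months | Did this arm hold its gain? | No | Yes, within one arm |
| Arm-by-visit contrast (not named) | Did the arm difference change? | Yes | Yes |

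Only the last row compares the arms on durability.

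**3. How large the dropout bias could be.** Assumptions, none from the document: standardised scores, correlation 0.6 between the earlier and the six-month score, and dropout that depends only on the earlier score. The bias in the attender-only six-month difference is then

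bias = 0.6 × (shift in the mean earlier score among treated children who stay − the same shift among controls who stay).

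Simulations with a true difference of 0.5 SD, 35 per arm and dropout driven by the two-week score gave:

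| Dropout pattern | Attender-only estimate (SD) | Approximate bias (SD) |
|---|---|---|
| 15% in both arms, same pattern | 0.49 | 0 |
| Worse children leave in both arms, 20% of controls and 10% of treated | 0.43 to 0.46 | 0.04 to 0.07 |
| 15% in both arms, score-related in one arm only | 0.37 to 0.42 | 0.08 to 0.13 |
| 20% of controls leave (doing badly), 10% of treated leave (doing well) | 0.23 to 0.34 | 0.16 to 0.27 |

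The ranges reflect how strongly dropout follows the score. A likelihood estimate that uses the earlier visits gave 0.49 to 0.51 throughout. A separate large-sample simulation with 15% leaving each arm found a bias of about 0 (same pattern), 0.08 (one arm only), and 0.16 to 0.25 (opposite directions).

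**4. Ceiling for the last row.** Suppose exactly the worst 20% of controls and exactly the best 10% of treated children leave. The mean earlier score of those who stay shifts by 0.350 SD and 0.195 SD, so the bias is 0.6 × (0.350 + 0.195) = 0.33 SD. The 0.27 figure is 0.27/0.33, about four-fifths of that, so it represents near-extreme selection.

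**5. Scale.** With 30 per arm, the standard error of a mean difference is √(2/30) = 0.26 SD. The moderate biases are a quarter to a half of one standard error, and the extreme one is about equal to it.

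**The case against.** The strongest case on the other side has five parts.

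**Durability is not wholly untested.** A reader might infer that no planned test addresses it. That goes too far. A two-sample test at six months compares the randomised arms on whether they still differ, which is one ordinary meaning of sustained benefit. A paired test from end of treatment to six months would speak to maintenance within an arm. An effect can also shrink and still be worth having. This stands. What is absent is a between-arm estimate of change.

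**The article does not say that each visit is tested separately on those who attend.** This is true. It assigns no test to a visit and is silent on analysis sets and missing data, which an article may leave to the full protocol or analysis plan. That silence is not criticised here. The point concerns the tests that are named, and attender-only use is how those tests normally run.

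**The 15% is not a six-month rate.** It is one overall planning figure, and the inclusion criteria ask families to commit to follow-up. Placing all of it after the two-week visit is an assumption.

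**The large bias needs an unlikely pattern.** A reader might take a fall from 0.50 to 0.23 SD as the expected distortion. The documents give no support for that: the correlation, the effect size, the 20%/10% split and the opposite directions are all assumed. Dropout was also made to depend only on an observed score, so the likelihood estimate recovers the truth by construction.

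**The outcome-by-visit schedule is in a figure that is not shown.** The ultrasound measures may not be taken at every visit. This limits which outcomes the remedy applies to.

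**Conclusion.** The concern holds in a limited form. The article itself fixes the tests, and they do not match the purpose it gives to follow-up: none compares the arms on how the effect changes between the end of treatment and six months. That conclusion rests on the text alone.

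The dropout part is conditional. It assumes that the named tests are run on available values and that dropout follows earlier scores differently in the two arms. With an assumed between-visit correlation of 0.6, the six-month difference is off by about 0 when dropout works alike in both arms, by roughly 0.07 to 0.13 SD in moderate cases, and by up to about 0.27 SD under strong opposite selection. Bias is possible, not established.

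The change is worth making because it is cheap. The stated tests do not make the trial's six-month comparison invalid.

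**What to change.** For each continuous outcome measured at more than one post-treatment visit, replace the separate t-tests with one linear mixed model:

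- **Terms:** baseline value, arm, visit, arm-by-visit and baseline-by-visit, with an unstructured covariance over visits.
- **Children:** every randomised child with at least one post-treatment value.
- **Report:** the arm difference with its 95% CI at each visit, and the change in that difference from end of treatment to six months as the between-arm durability estimate.
- **Paired tests:** keep as description only.

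The cost is analysis wording. No new data or visits are needed, and the stated software fits the model. With three post-treatment visits the covariance has six parameters (three variances and three covariances).

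There are two limits to state openly. The model relies on data being missing at random given baseline, arm and the scores already observed, which is a weaker assumption than attender-only tests need. The durability estimate will also be imprecise. With 30 per arm, correlation 0.6 and equal SDs, its standard error is about √(2 × 2 × (1 − 0.6)/30) = 0.23 SD, so the 95% CI is about ±0.45 SD. It should be read as an estimate with its interval, and a non-significant change should not be taken as proof that the effect lasted.

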## Discussion

The multifactorial causes of atlanto-axial rotatory subluxation (AARS) are a multifactorial condition involving complex biomechanical and pathological mechanisms. Figure 4 shows the normal atlantoaxial joint x-ray image and AARS image. Current treatment options are divided into surgical and conservative approaches (36). Interestingly, traditional Chinese medicine techniques, such as manipulation and bone-setting, have shown clinical effectiveness in treating AARS (37). One notable method is the gentle muscle adjustment technique, which is performed while maintaining continuous traction. This technique is based on the principle of “equal emphasis on muscles and bones, prioritizing muscles.” It creates a localized state of “instability” in the cervical area through traction. The method involves manipulation and dynamic adjustments across six movement axes. These actions restore the normal muscle tone and function, ultimately achieving proper skeletal alignment. The main goal of this approach is to restore the ecological balance between muscles and bones in the atlanto-axial joint. This enhances stability and reduces the risk of recurrence, and thus may provide new insights for the clinical therapy of pediatric AARS.

**Figure 4 F4:**
[figure not shown]
**(A)** Normal atlantoaxial joint x-ray image; **(B)** AARS x-ray image.

The current standards for evaluating treatment efficacy primarily depend on subjective assessment scales, which do not provide objective metrics to evaluate treatment effectiveness. The introduction of MUSU technology offers a chance to quantitatively evaluate the effects of the soft tissue manipulation method under continuous traction on cervical muscles, focusing on aspects such as muscle morphology and elasticity (38, 39). This approach aims to investigate the connection between the characteristics of neck muscles and the occurrence of neck pain and functional limitations. Such advancements present a more objective, safe, and cost-effective way to assess clinical outcomes.

However, despite the established effectiveness of the soft tissue manipulation technique combined with continuous traction, research into AARS (Acute Anterior Radial Syndrome) has been in its early stages, marked by significant gaps and a lack of rigorous clinical trials, many of which often rely on anecdotal evidence. Additionally, there is a shortage of evidence-based treatment protocols and randomized controlled trials, which diminishes the reliability of the outcomes reported in existing studies.Our research is based on muscle-bone theory. It involves a randomized controlled trial aimed at assessing the effectiveness of traction along with manipulation and bone-setting for AARS, making it a groundbreaking clinical effort in this field. We expect that the results of this study will provide new insights and approaches for treating conditions related to AARS. Ultimately, we hope that the findings from this trial will help reduce the symptoms experienced by individuals with AARS, lessen their physical and psychological burdens, and improve their overall quality of life.

## Limitations

This study could not be conducted as a fully blinded trial, which introduced bias into the results. We have will highlight the risk of bias and its potential impact in the clinical findings. Future clinical research may benefit from more precise design regarding the implementation of blinding methods. It is worth noting that the musculoskeletal ultrasound examination method mentioned herein also possesses certain limitations. As a relatively novel clinical assessment technique for measuring muscle strength, musculoskeletal ultrasound relies heavily on the operator's technical proficiency and knowledge base. Furthermore, the image quality produced by the ultrasound machine may introduce bias into the muscle measurement results.

## Conclusion

In summary, this study proposes to employ the method of gentle tendon adjustment under continuous traction as the treatment approach, targeting pediatric patients with AARS. A clinical randomized controlled trial methodology will be adopted to observe changes in visual analogue scale (VAS) pain scores, neck disability index (NDI) scores, and alterations in cervical muscle morphology and elasticity before and after treatment. By objectively quantifying clinical efficacy through musculoskeletal ultrasound during sustained traction with gentle tendon manipulation, this study will clarify the clinical value of this approach for treating pediatric AARS, facilitating its future implementation.
